### Sample size calculation

The study has been powered to detect a reduction of 20% of morphine consumption outcome between the study and placebo groups. Data from the head and neck surgery department of the Croix-Rousse Hospital permitted an estimation, in the absence of lidocaine administration, of a mean morphine consumption of 43 mg at day 2 (standard deviation 17 mg). With a statistical power of 0.80, 114 patients (57 per group) will be needed to demonstrate such a difference (Student’s *t* test). To compensate for a possible dropout of 10% of patients, it is planned to include a total of 128 patients (64 per group).

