### Data analysis

Data will be analyzed according to the intention-to-treat principle. Unblinding is planned at the end of the study, after a database freeze. A descriptive analysis will first be performed. The data will be presented as counts and percentages for qualitative data, as means and standard deviation for normally distributed quantitative data, or as medians and interquartile range for non-normally distributed variables. The analysis of the main outcome (cumulative morphine consumption in the first 48 postoperative hours) will be performed using Student’s *t* test. A multivariate linear regression analysis will also be performed to identify factors independently associated with morphine consumption 48 h after surgery. The factors studied will be the type of surgery, tumor site, stage of cancer, duration of the surgery, NRS score upon arrival in the PACU, use of preoperative analgesic, and use of high-dose intraoperative remifentanil. During surgery, intraoperative remifentanil consumption as well as morphine consumption in the 24 postoperative hours will be compared between the two groups using Student’s *t* test. The incidence of postoperative chronic pain will be compared between the two groups and the factors potentially associated with the occurrence of chronic pain will be analyzed by logistic regression. Subgroup analysis will be performed to compare patients with and without major pectoralis flap or free flap. The statistical analyses will be carried out under the responsibility of the methodologist of the clinical research center of the Croix-Rousse Hospital. All analyses will be conducted using SPSS software version 19.0 (IBM Corp., Armonk, NY, USA) and R software (R Development Core Team, Vienna, Austria). A value of *p* < 0.05 will be considered statistically significant.

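### 57 patients per group give about 76% power, not 80%, for the stated 20% reduction in 48-hour morphine consumption

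*Protocol article*

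**What the plan says.** The section "Sample size calculation" of the protocol article sets the target: "The study has been powered to detect a reduction of 20% of morphine consumption outcome between the study and placebo groups". For patients not given lidocaine it takes, from departmental data, "a mean morphine consumption of 43 mg at day 2 (standard deviation 17 mg". It then states the result, naming Student's t test as its basis: "With a statistical power of 0.80, 114 patients (57 per group) will be needed to demonstrate such a difference". Finally it adds the allowance for loss: "To compensate for a possible dropout of 10% of patients, it is planned to include a total of 128 patients (64 per group".

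The section gives no alpha, no absolute difference in mg and no mean for the lidocaine group. The section "Data analysis" names the same t test for the primary outcome and sets the threshold: p "< 0.05 will be considered statistically significant". Neither section says whether the test is one-sided or two-sided.

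**The concern.** The section prints all the inputs except the sidedness of the test, so the result can be recalculated, and the printed result does not follow from the printed inputs. This is not detail left to a fuller document: input and output stand in the same paragraph and disagree.

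What is at stake is how the primary result will be read. If the trial finds no significant difference, readers will judge that against an 80% chance of detecting a 20% reduction. If the planned number of evaluable patients does not give that chance, the null result will look more informative than it is.

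**Working it through.** **Inputs.** From "Sample size calculation": control mean 43 mg, SD 17 mg (the only one given, so taken as common to both groups), 20% reduction, power 0.80, Student's t test, equal groups, 10% dropout. From "Data analysis": significance level 0.05. Two-sided testing is assumed first; the one-sided case follows.

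**Effect size.** Difference = 0.20 × 43 = 8.6 mg. Standardised effect d = 8.6 / 17 = 0.506.

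**Sample size, normal approximation.** n per group = 2 × (1.960 + 0.842)² / d² = 2 × 7.849 × (17 / 8.6)² = 61.3, so 62.

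**Sample size, t test (noncentral t).** n = 62.3, so 63 per group, 126 in total. The article states 57 and 114.

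**Power for 8.6 mg, t test, two-sided 0.05:**

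| Evaluable per group | Power |
|---|---|
| 57 | 76.3% |
| 60 | 78.5% |
| 62 | 79.8% |
| 63 | 80.4% |
| 64 | 81.1% |

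The normal approximation gives 77.1% at 57 per group, so the choice of formula does not explain the gap.

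**Other readings of the stated inputs:**

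- One-sided 0.05: n = 49.0 by the t test (48.3 by the normal approximation), so 49 to 50 per group. Power at 57 would be 85%.
- SD proportional to the mean (17 mg and 13.6 mg): 50.3, so 51 per group.
- Log-normal data compared as a ratio: 45.8, so 46 per group.

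None gives 57.

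**What does give 57.** With a 9 mg difference and a two-sided test, the t test gives n = 56.98, so 57, with power 0.800. The normal approximation gives 2 × 7.849 × (17 / 9)² = 56.01, also 57. Conversely, the difference detectable with 80% power at 57 per group is 9.00 mg, and 9.00 / 43 = 20.9%. A 20% reduction puts the lidocaine mean at 43 − 8.6 = 34.4 mg. Rounding that to 34, or 8.6 to 9, reproduces the article's figure. A one-sided test for 8 mg (18.6%) also gives 57 (n = 56.5), but needs two inputs that appear nowhere.

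**Dropout step.** 57 / 0.9 = 63.3, so 64 per group and 128 in total. This step is correct. In reverse, 64 × 0.9 = 57.6, so the planned loss returns the trial to 57 or 58 per group.

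**The case against.** There are four arguments on the other side.

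- **The inputs are rounded.** Mean and SD are printed as whole milligrams. A mean of 43.3 and an SD of 16.5 print as 43 and 17 and give n = 56.99 by the normal approximation. This does not carry over to the t test that the article names: those values give 58.0, and even 43.49 and 16.51, at the favourable edge of both roundings, give 57.5, which rounds up to 58. The objection justifies saying that the figure fails on the inputs as printed; it does not restore the figure.
- **Sidedness is not stated.** Under a one-sided 0.05 test, 57 per group would have 85% power and there would be no shortfall. That is correct, and the 76% depends on the two-sided reading. But 57 would then not be the number needed for 0.80, so the statement still fails.
- **Loss may be below 10%.** The primary outcome is morphine over 48 hours in hospital and the analysis is by intention to treat. The only distant visit, at 3 to 6 months, serves a secondary outcome. This is a fair point: 57 per group is the planned case, not a certain one. Even so, 80% power needs 63 of the 64 in each group, so it tolerates the loss of one patient per group where the plan allows for six or seven.
- **The effect is small.** The shortfall is under 4 percentage points, the test and the analysis set do not change, and a confidence interval will show the precision achieved. This stands, and it argues for a light correction rather than for leaving the statement as it is.

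**Conclusion.** The concern holds. From the printed mean, SD and percentage reduction, a two-sided t test at 0.05 needs 63 evaluable patients per group. The stated 57 gives 76.3% power, a type II error of 23.7% instead of 20%. At 57 per group the trial has 80% power for 9.0 mg (20.9%), not for 8.6 mg (20%).

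The power figure rests on a common SD of 17 mg and on the conventional two-sided reading of p < 0.05. The failure to reproduce 57 does not depend on sidedness. That the cause was rounding the target to 9 mg is an inference, though it fits exactly.

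**What to change.** Correct the sample size section without changing enrolment. State that alpha is two-sided 0.05, if that is what was intended, give the difference in mg, and report the power the design has. For example:

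*With 64 patients per group randomised and 10% loss (57 per group analysed), a two-sided alpha of 0.05 and an SD of 17 mg, the trial has 76% power to detect a 20% (8.6 mg) reduction and 80% power to detect a 9.0 mg (20.9%) reduction. With no loss, power for 8.6 mg is 81%.*

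If the calculation used unrounded departmental data, print those values instead and recompute the power from them. The cost is wording only; the stated power becomes slightly less favourable. The alternative of keeping 80% power for 8.6 mg after 10% loss would take 63 / 0.9 = 70 per group, or 140 in total, which is 12 more than planned. The correction does not require this.

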### Protocol amendment

In order to extend inclusions, the protocol was amended (October 2016) to also include women, as well as patients undergoing total laryngectomy and interventions completed by free flap coverage.

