### Randomization

Patients will be allocated by randomized complete block design, stratified by center, to one of the two groups that will receive either intravenous lidocaine (study group) or placebo (placebo group) during the intraoperative and early postoperative period. The randomization will be processed by the investigator after the preoperative assessment, using a computer-generated list. Allocation concealment will be transmitted to the data manager and to each pharmacy department. Allocation will be ensured by enclosing the treatment unit in sealed, opaque, sequentially numbered envelopes prepared by the pharmacy department, which will be opened only upon arrival of the patient in the operation room by a nurse who will prepare the syringes. The nurse will prepare the treatment unit away from the operating room in order to keep the study participants blinded from the allocation. Preparations will consist of two 50-ml syringes for continuous infusion by syringe pump. Postoperative outcomes will be assessed by research personnel who will remain blinded to the type of intervention throughout the study.

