### Limits

The study does, however, have several limitations. One limitation is the recruitment of patients undergoing various types of procedure. Surgical techniques will be obviously different according to each procedure, and therefore we have planned subgroup analyses (with or without major pectoralis flap or free flap). Another limitation is that, for organizational issues, treatment units have to be prepared by a PACU nurse who then brings the syringe to the operating theater but who will not be involved in the care of the study patient. Although this aims to guarantee blinding, as the nurse and the medical team treating the patient will be in the same department then a bias due to unblinding cannot be ruled out. Furthermore, if use of postoperative corticosteroids was expected by the surgical team, the patient was not enrolled. However, if corticosteroids are infused in the perioperative period because of a potential upper airway edema, the patient will not be excluded; analyses conducted according to the intention-to-treat principle will be used for analysis, and sub-group analysis will be considered according to each group’s workforce.

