### Trial status

Patient recruitment started in December 2016. The predicted study completion date is June 2019.

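### The primary 48 h morphine comparison is fixed as an unadjusted t test, although adjustment for centre and planned flap could recover precision at almost no cost

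*Protocol article*

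**What the plan says.** All places are in the Protocol article.

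- **Protocol amendment:** "the protocol was amended (October 2016) to also include women, as well as patients undergoing total laryngectomy and interventions completed by free flap coverage".
- **Randomization:** "Patients will be allocated by randomized complete block design, stratified by center, to one of the two groups". Centre is the only stratification factor named.
- **Data analysis, primary test:** "The analysis of the main outcome (cumulative morphine consumption in the first 48 postoperative hours) will be performed using" Student's t test. No covariate is attached to this test.
- **Data analysis, regression:** "A multivariate linear regression analysis will also be performed to identify factors independently associated with morphine consumption 48 h after surgery". The listed factors are type of surgery, tumour site, cancer stage, duration of surgery, NRS score on arrival in the PACU, preoperative analgesic use and high-dose intraoperative remifentanil. Treatment group, centre and sex are not listed.
- **Data analysis and Limits:** "One limitation is the recruitment of patients undergoing various types of procedure". The response given there is a subgroup analysis of patients with and without a pectoralis major or free flap.
- **Sample size calculation:** "Data from the head and neck surgery department of the Croix-Rousse Hospital permitted an estimation" of the untreated mean (43 mg) and SD (17 mg). The case mix behind these figures is not given.

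**The concern.** The outcome is total morphine over 48 hours, compared across procedures that run from partial laryngectomy to free-flap reconstruction, and in both sexes. The article itself treats the operation as relevant: type of surgery heads the regression list, and flap defines the planned subgroups. Even so, the confirmatory test uses neither the operation nor the factor on which randomisation was stratified.

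If centre or planned procedure predicts morphine use, an unadjusted test leaves that variation in the error term. What is at stake is the width of the confidence interval and the power of a trial with little slack. The estimate stays unbiased.

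The two existing provisions do not close the gap. A subgroup analysis splits the sample and does nothing for the precision of the overall estimate. The regression is meant to find associated factors. As listed, it contains no treatment term, and three of its variables arise after randomisation: duration of surgery, PACU pain score and intraoperative remifentanil. Remifentanil consumption is also a secondary outcome that treatment may change, so conditioning on it could remove part of the effect of interest.

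**Working it through.** **Inputs from the article.** Target difference 20% of 43 mg = 8.6 mg; SD 17 mg; alpha 0.05 (sidedness not stated, two-sided assumed); power 0.80; 57 per group evaluable, 64 per group enrolled.

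**The plan's own figure.** n per group = 2 × (1.960 + 0.842)² × 17² / 8.6² = 61.3, so 62 (62.3 by the noncentral t, so 63). The stated 57 is not reproduced and gives about 76% power by the t test. The dropout step does reproduce: 57 / 0.9 = 63.3, so 64 per group and 128 in total. The shortfall at 57 is a separate matter; here it only sets the 76% reference point.

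**What is unknown.** The article gives no difference in 48 h morphine by centre, procedure, flap or sex. Two sets of assumptions bracket the question.

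*A. The SD of 17 mg already contains this variation.* If baseline covariates explain a share R² of the variance, the residual SD is 17 × √(1 − R²) and n per group is 61.3 × (1 − R²), ignoring the few degrees of freedom spent.

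| R² | Residual SD (mg) | n per group for 80% power | Power at 57 per group |
|---|---|---|---|
| 0 | 17.0 | 62 | 76% |
| 0.05 | 16.6 | 59 | 78% |
| 0.10 | 16.1 | 56 | 81% |
| 0.20 | 15.2 | 50 | 85% |

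*B. Flap variation comes on top of 17 mg.* With half the patients having a flap and means differing by D, the overall SD is √(17² + 0.25 × D²).

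| D (mg) | Overall SD (mg) | Unadjusted power at 57 per group |
|---|---|---|
| 0 | 17.0 | 76% |
| 5 | 17.2 | 75.5% |
| 10 | 17.7 | 73% |
| 15 | 18.6 | 69% |
| 20 | 19.7 | 64% |

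In B, adjustment for flap brings the SD back to 17 mg by construction, so the table illustrates the premise and is no evidence for it.

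**Validity of the t test.** A simulation with 57 per group, simple randomisation and a prognostic factor present in half the patients gave type I error of 5.1%, 4.9% and 5.0% for D = 0, 10 and 20 mg. The unadjusted test is valid.

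**Chance imbalance.** The SD of the difference in flap proportions between arms is √(2 × 0.25 / 57) = 0.094, a 95% range of about ±18 percentage points. With D = 10 mg this moves the estimate by up to about 1.8 mg. The standard error of the unadjusted difference is at least 17 × √(2/57) = 3.2 mg and already includes this source of variation.

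**The case against.** The strongest reply is that a centre-stratified trial of 128 patients analysed by t test is valid, that the article openly acknowledges the procedure mix, and that covariate adjustment is commonly left to an analysis plan that is not shown. The first two parts stand: there is no error of validity and nothing is concealed. The third does not remove the point, because the article does not leave the primary test open. It names Student's t test.

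A reader might infer more than the documents support:

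- **That procedure or sex is a strong source of variation.** No figure supports this. Limits says only that techniques differ, and body weight by sex is not reported. At D = 5 mg the loss under assumption B is under one percentage point.
- **That the amendment made the planning SD too small.** The article does not say whether 17 mg covers the added groups; it may already include them. The amendment added free flaps; pectoralis major flaps are eligible but are not among its additions, so the whole flap contrast cannot be charged to it.
- **That the population changed mid-trial.** "Patient recruitment started in December 2016", after the October 2016 amendment.
- **That chance imbalance is an additional harm.** Under randomisation it is already in the standard error.
- **That the subgroup analysis is the only response to the procedure mix.** The regression also includes type of surgery, although it cannot serve as the adjusted treatment effect.
- **That randomisation should be re-stratified.** With completion predicted for June 2019 this could be a late trade-off, and adjustment does not need it.

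**Conclusion.** The point holds as one of efficiency. The stated primary analysis ignores both the stratification factor and a procedure characteristic that the trial already uses to define subgroups, and no other planned analysis gives an adjusted treatment effect. The result is an avoidable loss of precision if those factors predict morphine use.

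The size cannot be fixed from the documents. The two sets of assumptions run from negligible (D = 5 mg) to about 12 percentage points of power (76% to 64% at D = 20 mg, nearly half the 43 mg mean), or a saving of 3 to 12 patients per group if the covariates explain 5% to 20% of the existing variance. None of these figures is an expected loss.

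**What to change.** Before database freeze and unblinding, specify the primary comparison as a linear model (ANCOVA) of cumulative 48 h morphine on treatment group. Adjust it for centre and for planned flap (pectoralis major or free flap, yes/no). Take flap as planned preoperatively, not as performed. Sex may be added as a further baseline covariate. Report the adjusted mean difference in mg with its confidence interval, and keep Student's t test as a sensitivity analysis.

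State that no post-randomisation variable enters this model, and keep the listed regression as a separate exploratory analysis.

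The cost is two degrees of freedom, or three with sex, and a change of wording. The article does not say that planned flap is recorded as a trial variable; if it is not, it has to be taken from preoperative records without knowledge of allocation. Randomisation and enrolment stay unchanged.

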## Discussion

### Benefits

Recently, intravenous lidocaine has been shown to effectively control postoperative pain according to the surgical procedure. Pain relief is reported to persist for 48 h after infusion [8]. There are no published data regarding systemic lidocaine in major head and neck cancer surgery. We hypothesized that perioperative intravenous lidocaine would lead to opioid sparing and CPSP reduction.

The benefit of lidocaine for pain relief is not likely to be due to sodium channel blockade regarding the perioperative relatively low blood concentrations [8]. It may therefore be related to a priming blockade of granulocytes, which could limit the exaggerated release of cytokines and reactive oxygen species [27], even effective at very low concentration [28].

Lidocaine is widely used intravenously in the perioperative period for abdominal and urological procedures and could lead to opioid sparing, through analgesic and anti-inflammatory properties [8]. Moreover, by an antihyperalgesic effect, systemic lidocaine could prevent CPSP [3–5]. Assessment of hyperalgesia and CPSP is permitted as we tried to limit the use of antihyperalgesic drugs (such as nitric oxide, ketamine, and nonsteroidal anti-inflammatory drugs) [21–23].

Moreover, surgery-induced stress and anesthetic-induced and opioid-induced immunosuppression during the perioperative period may play a critical role in the establishment and growth of metastatic lesions. The role of anesthetic-induced immunosuppression in the promotion of cancer recurrence is suggested by currently available preclinical studies [29] (Additional file 1).

### Risks

Medical care of the included patients, in terms of anesthesia, surgery, and postoperative care, will not differ from routine practice. Risks are mainly related to the systemic toxicity of local anesthetics; an overdose may affect the central nervous system (e.g. drowsiness, confusion, euphoria, double vision, seizures), the cardiovascular system (e.g. hypotension, bradycardia, arrhythmias, cardiac arrest), the respiratory system (e.g. tachypnea, apnea), or the blood system (e.g. methemoglobinemia). However, the doses used in the present study have been repeatedly demonstrated to be safe and to result in plasma concentrations that are far below the toxic level (5 μg.ml^− 1^) [8]. As a safety measure, patients with cardiac systolic dysfunction or impaired lidocaine metabolism due to liver dysfunction or cirrhosis are excluded from the study [6]. Moreover, patients are continuously monitored by electrocardiography during the administration of lidocaine. If intoxication is suspected, the patient will receive an infusion of lipid emulsion after standard resuscitative measures according to local protocols based on international guidelines [30].

### Limits

The study does, however, have several limitations. One limitation is the recruitment of patients undergoing various types of procedure. Surgical techniques will be obviously different according to each procedure, and therefore we have planned subgroup analyses (with or without major pectoralis flap or free flap). Another limitation is that, for organizational issues, treatment units have to be prepared by a PACU nurse who then brings the syringe to the operating theater but who will not be involved in the care of the study patient. Although this aims to guarantee blinding, as the nurse and the medical team treating the patient will be in the same department then a bias due to unblinding cannot be ruled out. Furthermore, if use of postoperative corticosteroids was expected by the surgical team, the patient was not enrolled. However, if corticosteroids are infused in the perioperative period because of a potential upper airway edema, the patient will not be excluded; analyses conducted according to the intention-to-treat principle will be used for analysis, and sub-group analysis will be considered according to each group’s workforce.

